### Economic analysis

From a societal perspective, we will perform an economic analysis alongside the cohort study and clinical trials. The data on cancellation rates, FSH consumption and pregnancy rate from the cohort study (900 couples) and the two RCTs (300 patients per study) will be integrated in a cost-effectiveness analysis. We will build on previous work that we have done for CVZ (College Voor Zorgverzekeringen; College of Health Insurances). In the analysis, we will assess the cost-effectiveness of using an ORT for dose adjustments in poor responders ór hyperresponders only and using an ORT for dose adjustment in both poor responders and hyperresponders, as compared to current practice where no ORT is used and standard FSH doses are given.

The study design will enable us to compare the costs and effects of the following strategies:

I. IVF or ICSI without an ORT for three cycles with a standard start dose (reference strategy)

II. ORT followed by IVF or ICSI with dose adjustment in women with predicted hyperresponse and predicted poor response

III. ORT followed by IVF or ICSI and dose reduction in women with predicted hyperresponse only

IV. ORT followed by IVF or ICSI and dose adjustment in women with predicted poor response only

The key question in the economic evaluation is to assess whether the health and associated economic benefits of individualised treatment of subfertile women in terms of increased ongoing pregnancy rates and reduced rates of hyperstimulation, outweigh the additional costs of an ORT. The economic evaluation will be designed as a cost-effectiveness analysis with the costs per pregnancy resulting in live birth within 18 months as the primary outcome measure. Cost-effectiveness of each strategy will therefore be expressed as costs per live birth. The incremental cost-effectiveness ratio (ICER) of each individualised dose-adjustment strategy as compared to a strategy with standard FSH dose will be estimated as the ratio between difference in costs between strategies and the difference in pregnancy rates, and reflects the extra costs required to obtain one additional live birth. If in the predicted poor response group individualised FSH treatment following an ORT increases the live birth rate without affecting OHSS rates, individualised treatment is the dominant strategy. If in the predicted hyperresponse group individualised FSH treatment following an ORT reduces the rate of OHSS, without affecting live birth rates, individualised treatment is the dominant strategy.

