**Discussion:**

The results of this study will be integrated into a decision model that compares cost-effectiveness of the three dose-adjustment strategies to a standard dose strategy. The study outcomes will provide scientific foundation for national and international guidelines.

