## Discussion

The number of patients starting IVF or ICSI treatment in the Netherlands annually is approximately 7,000 and they undergo 16,000 IVF or ICSI cycles a year [14]. Women with a poor response or hyperresponse comprise 30- 55.8% of the population [11,15]. Bouwman et al. [1] showed that hormonal stimulation is the most expensive part of IVF and ICSI treatment.

In modern society, many women delay childbearing, despite intensive and costly efforts to increase awareness of the unavoidable ovarian failure associated with advanced age. In the Netherlands, the age at which a woman delivers her first child has increased from 25.5 years (1980) to 29.4 years (2011) making Dutch women amongst the oldest mothers in the world [16]. As a result of this delayed child bearing, the most frequent indication for assisted reproductive techniques such as IVF and ICSI is now unexplained subfertility in couples with increased female age, in which diminished ovarian reserve is usually the cause. As a consequence, the potential value of an ORT is increasing.

A recently published Markov decision-analytic model showed that individualisation of the FSH dose according to ovarian reserve is likely to be cost-effective in women who are eligible for IVF or ICSI treatment [17]. The use of an ORT followed by individualised FSH regimens can have a large impact on current IVF practice. The advantages may include improvement of quality of life for the patient, reduction of harm associated with conventional IVF, increased effectiveness and reduction of costs.

The results of this study will be integrated into a decision model that compares cost-effectiveness of the three dose-adjustment strategies to the standard FSH dose strategy. The costs and the live birth rates of these strategies will be assessed. The study outcomes will provide scientific foundation for national and international guidelines.

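### The only ICERs defined compare each dose-adjustment strategy with the standard dose; none is the right ratio for choosing between adjusting in one group and adjusting in both

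*Protocol article*

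**What the plan says.** The Economic analysis section of the protocol article states that "The study design will enable us to compare the costs and effects of the following strategies", and lists four. Strategy I is the reference: no ORT and a standard start dose. Strategy II is "ORT followed by IVF or ICSI with dose adjustment in women with predicted hyperresponse and predicted poor response". Strategy III is "ORT followed by IVF or ICSI and dose reduction in women with predicted hyperresponse only", and Strategy IV adjusts in predicted poor responders only.

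The same section fixes the comparator of the ratio: the ICER "of each individualised dose-adjustment strategy as compared to a strategy with standard FSH dose will be estimated". Its aims use the same comparator ("as compared to current practice where no ORT is used and standard FSH doses are given"), and so do the Discussion part of the Abstract ("compares cost-effectiveness of the three dose-adjustment strategies to a standard dose strategy") and the main Discussion ("compares cost-effectiveness of the three dose-adjustment strategies to the standard FSH dose strategy").

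The article defines no ICER of II against III or IV, no ordering by cost and no rule on extended dominance. The two statements about a dominant strategy compare individualised with standard treatment within one predicted-response group, not one strategy with another.

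**The concern.** A clinic or guideline body can adopt only one of I to IV for the screened population. For mutually exclusive options, the relevant ratio for each is its extra cost and effect over the next less costly option that is still in contention. A ratio against a distant common reference is an average over several steps, and may be a ratio against an option that is itself dominated.

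This matters here because II is III and IV applied to different women, and the two halves differ. RCT 1 raises the FSH dose above 150 IU/day and RCT 2 lowers it, so drug costs move in opposite directions. The planned gains are 15 and 7 points. A saving in one half can therefore offset spending in the other within the II versus I ratio. The main Discussion says the results will underpin national and international guidelines, for which adjusting in one group, the other or both is the practical choice.

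**Working it through.** **The plan's own figures.** The protocol gives no ICER and no unit cost, so there is no economic figure to reproduce. The effects come from the Sample size calculation section: RCT 1 25% to 40% (15 points), RCT 2 35% to 42% (7 points). The statements built on them reproduce with the usual two-proportion formula without continuity correction: a total of 304 against the stated 300 for RCT 1, 592 against 600 for both trials together (30% to 41%), and power of 23.7% against the stated 24% for RCT 2.

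**Algebra.** Let sP and sH be the population shares of predicted poor responders and hyperresponders, cP and cH the cost changes per woman, eP and eH the changes in live birth rate, and t the ORT cost per screened woman.

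- II vs I = (t + sP·cP + sH·cH) / (sP·eP + sH·eH)
- IV vs I = (t + sP·cP) / (sP·eP) = cP/eP + t/(sP·eP)
- III vs I = (t + sH·cH) / (sH·eH) = cH/eH + t/(sH·eH)
- II vs III = cP/eP
- II vs IV = cH/eH

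The ORT cost cancels in the last two, because testing is already paid for in III and IV. With positive effects and t = 0, II vs I lies between cP/eP and cH/eH, and so below the ratio of the weaker half.

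**Numbers.** Assumed: cP = +1,500 and cH = -300 cost units, signs following the dose directions. Shares come from the meta-analysis quoted in the Sample size calculation section: 25% + 18% = 43% with AFC below 10, an approximation to the RCT 1 class of AFC below 11, and 24% with AFC above 15. The cost terms are 0.43 × 1,500 = 645 and 0.24 × (-300) = -72, total 573.

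With the protocol's effects and t = 0:
- II vs I: 573 / (0.43 × 0.15 + 0.24 × 0.07) = 573 / 0.0813 = 7,048
- II vs III: 645 / 0.0645 = 10,000, a ratio of 1.4

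With an assumed RCT 1 effect of 3 points and t = 0:
- II vs I: 573 / (0.0129 + 0.0168) = 573 / 0.0297 = 19,293
- II vs III: 645 / 0.0129 = 50,000, a ratio of 2.6

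In both cases III costs 72 less than I per screened woman and adds 0.0168 live births, so it dominates I, and a ratio of II against I is then not a decision ratio.

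**Adding an assumed ORT cost**, per screened woman:

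| RCT 1 effect | t | II vs I | IV vs I | II vs III |
|---|---|---|---|---|
| 15 points | 0 | 7,048 | 10,000 | 10,000 |
| 15 points | 50 | 623/0.0813 = 7,663 | 695/0.0645 = 10,775 | 10,000 |
| 15 points | 200 | 773/0.0813 = 9,508 | 845/0.0645 = 13,101 | 10,000 |
| 3 points | 0 | 19,293 | 50,000 | 50,000 |
| 3 points | 50 | 623/0.0297 = 20,976 | 695/0.0129 = 53,876 | 50,000 |
| 3 points | 200 | 773/0.0297 = 26,027 | 845/0.0129 = 65,504 | 50,000 |

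The two planned ratios bracket the step of interest: II vs I falls below it, and IV vs I equals it at t = 0 and exceeds it otherwise. With the protocol's effects, II vs I stays below II vs III until t reaches 0.0813 × 10,000 - 573 = 240.

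**Share of RCT 1 women.** The protocol plans on 20% (300 of 1,500) rather than 43%. With 20% and 24%, and t = 0, II vs I is (300 - 72)/(0.03 + 0.0168) = 4,872 against 10,000 for 15 points, and 228/0.0228 = 10,000 against 50,000 for 3 points. Over these four cases at t = 0 the gap runs from 1.4 to 5 times.

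**The case against.** A reader might infer that the plan hides a poor component, or that its output cannot inform the choice between groups. The document does not support that. III and IV are each set against I as well. In the 3-point example with no ORT cost, the planned output would show III dominant, IV at 50,000 and II at 19,293. The 50,000 is the very figure of the step from III to II. With positive effects, IV vs I is never below II vs III, and III vs I never below II vs IV, so these comparisons can make a half look worse but not better. The missing ratios could also be derived from the same costs and effects.

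Nor does the article set a threshold or a rule that II be adopted on its ratio against I. Its key economic question is whether the benefits outweigh the cost of an ORT, and comparisons with I address that. It does not exclude other comparisons and says in general terms that costs and effects of the strategies can be compared. Every cost above is assumed, and the larger gap depends on an RCT 1 effect far below the planned 15 points.

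All of this stands, and it limits the point. It does not remove it. Details such as a frontier plot or a willingness-to-pay range may well sit in a fuller document, and their absence is no finding. The comparator, however, is not left open: it is stated for the ICER and repeated in three further places. The ratios against I also do not give the uncertainty of the incremental step.

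**Conclusion.** The point holds as a poor choice of comparator, not as a loss of information. The ICER is defined only against Strategy I, although I to IV are mutually exclusive and II combines III and IV. II versus I is a blend that can be more favourable than adding the weaker half, while III versus I and IV versus I charge the whole ORT cost to a single group. None of the three is the ratio for deciding between one group and both.

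The blending and the cancelling of the ORT cost are algebra and do not depend on any assumed cost; the size does. With the protocol's effects and the costs and shares assumed above, the gap is modest (7,048 against 10,000). It grows to 19,293 against 50,000 if the RCT 1 gain is only 3 points. A large enough ORT cost would close or reverse it. The sample size and the clinical primary outcome are not affected.

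**What to change.** In the Economic analysis section, replace the sentence that defines the ICER with a sequential incremental analysis: order Strategies I to IV by cost, remove dominated and extendedly dominated ones, and report the ICER of each remaining strategy against the next less costly one, with its uncertainty, or as net benefit. Show II versus III and II versus IV explicitly, whichever of them lies on the frontier. Keep II, III and IV versus I, labelled as answering whether an ORT is worthwhile at all. Align the comparator wording in the Abstract and the main Discussion.

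The cost is a little more analysis in the same decision model. No new data and no change of design are needed.

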#### Experimental group

All women in the experimental group will receive an individualised FSH dose based on their AFC. If women in RCT 1 are randomised for dose adjustment they will use 450 IU FSH/day if the AFC is below 8 and 225 IU FSH/day if the AFC is 8-10. Women in RCT 2 will receive 100 IU FSH/day if they are randomised for dose adjustment. Participants will be subjected to the assigned dosage in the subsequent cycles. In RCT 1, dose adjustments are not allowed in a subsequent cycle. For women in RCT 2, dose adjustment in the second or third cycle is allowed, and can consist of a step of 25 IU FSH/day, if there is a poor response or hyperresponse (poor response is defined as the retrieval of less than five oocytes or the cancellation of a stimulation cycle because less than two follicles above 12 mm in diameter are observed on ultrasound; hyperresponse is defined as the retrieval of more than 15 oocytes or cancellation of a stimulation cycle because more than 20 follicles over 12 mm in diameter are growing and estradiol levels exceed 11.700 pmol/L (= 3187,08 ng/L) or if more than 30 follicles over 12 mm are growing).

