#### Control group

All women in the control group will receive a standard FSH dose of 150 IU/day, independent of the AFC classification. They will be subjected to the assigned dosage in the subsequent cycles. However, based on the response in preceding cycles, a dose adjustment in the second and third cycle is allowed, but cannot exceed a step of 50 IU FSH/day, if there has been a poor response or hyperresponse (as defined above).

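### The dominance rule for predicted poor responders has no cost condition, so a more effective but costlier regime could be labelled dominant

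*Protocol article*

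**What the plan says.** All places are in the protocol article.

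- **Economic analysis, rule for predicted poor responders.** If individualised dosing "increases the live birth rate without affecting OHSS rates, individualised treatment is the dominant strategy".
- **Economic analysis, rule for predicted hyperresponders.** If individualised dosing "reduces the rate of OHSS, without affecting live birth rates, individualised treatment is the dominant strategy".
- **Economic analysis, framework.** Just before these two sentences, the section makes cost per live birth within 18 months the economic outcome. It defines the ICER of each dose-adjustment strategy against the standard dose as the cost difference divided by the difference in pregnancy rates. The key question is whether the benefits "outweigh the additional costs of an ORT"; the extra FSH is not named there.
- **Experimental group.** Women in RCT 1 allocated to dose adjustment: "they will use 450 IU FSH/day if the AFC is below 8 and 225 IU FSH/day if the AFC is 8-10". Their dose is then fixed: "In RCT 1, dose adjustments are not allowed in a subsequent cycle".
- **Control group.** "All women in the control group will receive a standard FSH dose of 150 IU/day, independent of the AFC classification". After a poor response or hyperresponse, "a dose adjustment in the second and third cycle is allowed, but cannot exceed a step of 50 IU FSH/day".
- **Discussion.** An earlier cost study is cited as showing that "hormonal stimulation is the most expensive part of IVF and ICSI treatment".
- **Sample size calculation.** A net gain in pregnancy rate below 11% is judged unlikely to make testing plus dose adjustment cost-effective.

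**The concern.** In a cost-effectiveness analysis, one strategy dominates another when it is at least as effective and no more costly, and strictly better on at least one of the two. The poor-responder rule tests live births and OHSS only. It is worded as a complete conditional, and no other section supplies the missing cost condition.

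The omission falls where cost is most open to doubt. RCT 1 is the trial in which the individualised regime raises the assigned FSH dose. More effect at more cost is exactly the situation for which an ICER is computed.

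Cost-effectiveness is the stated aim of the study, and the results are meant to inform guidelines. To a payer, the word dominant means that there is no trade-off to weigh. Under this rule the word could attach to a regime for which there is one.

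**Working it through.** **1. The rule against the standard definition**

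| Condition | Standard dominance | Poor-responder rule | Hyperresponder rule |
|---|---|---|---|
| Effect | no worse | live births up, OHSS unchanged | OHSS down, live births unchanged |
| Cost | no higher | not stated | not stated |
| At least one strictly better | yes | yes, on effect | yes, on OHSS |

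**2. Assigned starting dose in RCT 1** (Experimental group, Control group)

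Ratio = individualised daily dose / control daily dose.

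- AFC below 8: 450 / 150 = 3.0
- AFC 8-10: 225 / 150 = 1.5

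For comparison, RCT 2: 100 / 150 = 0.67.

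**3. Three-cycle mean, allowing for control-arm steps**

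Assumption: three cycles in each arm with equal stimulation days. The experimental dose is fixed, so the ratio is 3 × individualised dose / sum of the control doses.

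| Control path (IU/day) | Sum | AFC below 8: 1,350 / sum | AFC 8-10: 675 / sum |
|---|---|---|---|
| 150, 150, 150 | 450 | 3.0 | 1.5 |
| 150, 200, 200 | 550 | 2.45 | 1.23 |
| 150, 200, 250 | 600 | 2.25 | 1.13 |

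The last path applies only if the text permits a second step. In its third cycle the AFC 8-10 ratio is 225 / 250 = 0.9, although the three-cycle mean stays above 1. A control step down after a hyperresponse would raise the ratios instead.

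**4. Extra FSH per cycle at the starting doses**

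The article gives no stimulation length; 8 to 12 days is an assumption.

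- AFC below 8: (450 - 150) × 8 to 12 = 2,400 to 3,600 IU
- AFC 8-10: (225 - 150) × 8 to 12 = 600 to 900 IU

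**5. What a cost condition would change**

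The article gives no prices, so net cost cannot be computed. For illustration, take the gain assumed for RCT 1 (25% to 40%, so 0.15) and a net extra cost per woman of 500 to 3,000 currency units, which is purely an assumption:

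- 500 / 0.15 ≈ 3,300 per additional live birth
- 3,000 / 0.15 = 20,000 per additional live birth

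The rule as written would label every case in this range dominant if OHSS were unchanged. Under the standard definition none of them is, and each is judged by its ICER.

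**6. Consistency with the rest of the article**

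The poor-responder rule sets no minimum gain, so any rise in live births meets its first condition. The Sample size calculation says that a net gain below 11% is unlikely to be cost-effective. That figure concerns both RCTs together, so it is not a threshold for RCT 1 alone. It does show that the authors accept that a positive effect can fail on cost.

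**The case against.** The strongest reply is that the economic analysis is sound apart from two sentences. The ICER is promised for each strategy without conditions. Outcome measures counts gonadotrophins among the resources, and the Economic analysis section brings FSH consumption into the model. Any extra drug cost would therefore show in the reported results. This stands, and it limits the point to the label.

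Four stronger readings are tempting, and the article does not support them:

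- **A reader might infer that no ICER would be weighed.** Nothing in the dominance sentence switches the ICER off.
- **A reader might infer that strategies II and IV would be declared dominant whenever RCT 1 shows more live births.** The sentence is confined to the predicted poor response group and also requires unchanged OHSS. The strategies cover the whole screened population, and strategy II depends on the hyperresponders too. No text carries the subgroup label over to a strategy.
- **A reader might infer that women in the individualised arm use 1.5 to 3 times the FSH overall.** Those ratios are for the assigned starting dose. Total use also depends on control-arm steps, stimulation days, cancellations and the number of cycles.
- **A reader might infer that the individualised regime is shown to cost more.** It is not. No prices are given, and earlier pregnancies or fewer cancellations could offset the drug cost.

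For hyperresponders the reply is stronger still. A lower starting dose and less OHSS make a saving plausible, although the cost of the test is still not checked.

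The absence of bootstrap methods or acceptability curves is no fault here, since an article may leave these to the full plan.

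**Conclusion.** The point holds as a defect in the stated dominance rule. The poor-responder sentence omits the cost condition and conflicts both with the ICER defined in the same section and with the remark on the 11% gain in the Sample size calculation. It does so in the group where the starting dose is 1.5 or 3.0 times control, or about 1.1-1.2 and 2.3-2.5 as a three-cycle mean if controls step up, assuming equal stimulation days.

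The consequence is a possible false label of dominance beside a correctly computed ICER. Whether the label would in fact be false depends on net cost, which the article does not allow to be calculated. The hyperresponder sentence shares the omission and is secondary. The randomised comparison, the primary clinical outcome and the sample size are unaffected, and no view is taken on any dose.

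**What to change.** Reword both dominance sentences in the Economic analysis section along these lines:

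- A strategy is called dominant only if its mean total societal cost, including the ORT and FSH, is no higher than that of the reference strategy and its live birth rate is no lower, with at least one of the two strictly better.
- If it is more effective and more costly, the conclusion rests on the planned ICER per additional live birth.
- OHSS enters through its costs and is also reported as a separate safety outcome.

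It would help to name the extra FSH next to the ORT in the key question.

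The cost is a change of wording. The resource and cost data are already planned, and no patients, visits or procedures are added.

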## Methods

### Study design

The OPTIMIST trial is a nationwide multicentre RCT. The cohort will consist of 1,500 women screened for ovarian reserve by an AFC prior to IVF or intracytoplasmic sperm injection (ICSI) treatment. Two RCTs are embedded in this cohort. Based on the AFC, women will be classified into four categories; AFC less than 8 (predicted poor responders), AFC 8-10 (predicted low-normal responders), AFC 11-15 (predicted normal responders) or AFC above 15 (predicted hyperresponders). RCT 1 will contain 300 women with an AFC below 11; RCT 2 will contain 300 women with an AFC of more than 15. A total of 25 academic and non-academic centres in the Netherlands will participate. An economic analysis is incorporated to assess the cost-effectiveness of an ORT and subsequent individualised FSH dosage in IVF or ICSI treatment. Inclusion was started in May 2011. This study will be conducted in accordance with the principles of the Declaration of Helsinki and in accordance with Good Clinical Practice. The study protocol has been approved by the Institutional Review Board (IRB) of the University Medical Center Utrecht (MEC 10-273) and by the board of directors of all participating centres.

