### Sample size calculation

Based on the expected gain in pregnancy rate resulting in live birth as reported in the study by Popovic-Todorovic et al. [12], we expect an increase in pregnancy rate over three IVF or ICSI cycles of 15% (from 25% to 40%) in the predicted poor responders (RCT 1). To demonstrate that such a difference will occur, we need to include 300 couples in RCT 1 (alpha-error of 0.05 and a power of 80%, two-sided test). If we expect a positive effect of dose adjustment in both the predicted poor responders (RCT 1) and predicted hyperresponders (RCT 2), the total sample size of 600 women, in both RCTs, allows the detection of an increase in pregnancy rate from 30% after conventional treatment to 41% in the dose adjustment group (alpha-error of 0.05 and a power of 80%, two-sided test). If the net effect of dose adjustment on pregnancy rate is less than 11%, it is unlikely that an ORT and dose adjustment is cost-effective. The assumed 30% success rate in the conventional group in the latter calculation is higher than the assumed 25% success rate in the conventional group of solely RCT 1, as RCT 1 only contains women with an expected poor response. RCT 2 adds women with a predicted hyperresponse, who are expected to have higher pregnancy rates. For RCT 2 an increase in pregnancy rate from 35% to 42% over three cycles is expected. With 300 participants the power to detect this difference is 24%.

In our Individual Patient Data meta-analysis on 2,300 patients in 13 studies, we found that 25% had and AFC below 6, 18% had an AFC between 6 and 9, 33% had an AFC between 10 and 15 and 24% had an AFC of more than 15 [12].If we assume that 20% of the couples will have a low or low-normal ovarian reserve, and are therefore eligible for the predicted poor responder trial, we need to include a cohort of 1,500 women for ovarian reserve screening in order to achieve the necessary number of participants for the two trials. This will then allow a sample size of just over 300 women for RCT 1.

A sample size calculation for the cost effectiveness analysis is not provided. It is generally accepted that this type of sample size is not provided because the uncertainty of the cost economy ratio is largely determined by the variation in the efficacy (the denominator of the ratio) and can therefore not be performed at a realistic level.

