### Recruitment, consent and randomisation

Eligible women with an indication for a first IVF or ICSI treatment cycle or a first IVF or ICSI treatment cycle after birth of a child will receive oral and written information from their attending physician. The investigator will explain the study fully and in sufficient detail to allow the women to make an informed decision whether to participate or not. If a woman is willing to participate, written informed consent will be obtained. Based on AFC classification women will be entered into one of the four AFC classes (see Figure 1). Participants, excluding the predicted normal responders, will be randomly allocated to a standard or individualised FSH regime. All predicted normal responders will receive the standard dosage. Randomisation will be performed centrally by a web-based randomisation program and will be stratified by centre.

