#### Statistical analysis

SPSS and Excel will be used to perform the statistical analysis. A probability (p) of less than 0.05 will be considered to be significant. Data will be presented for all arms of the study group. Data will be expressed as means ± standard deviation and proportions or rates. The analysis will be by intention to treat.

Descriptive analysis will be used to describe the primary and secondary outcome variables and to compare these outcome variables among the treatment arms of the two RCTs. Comparisons between the two arms of the randomised group will be done by applying Chi/square testing to crude rates of cumulative implantation and ongoing pregnancy and by using life table analysis to account for the factor of time to implantation or pregnancy. The relative contribution of predictive factors of success in any of the treatment arms, such as female age and duration of subfertility will be assessed by univariate and multivariate logistic regression and Cox regression.

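### The dominance rule for RCT 2 needs evidence of no loss in live births, but sets no margin or interval, and a p<0.05 test in 300 women cannot supply that evidence

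*Protocol article*

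**What the plan says.** The Economic analysis section fixes a conclusion for the predicted hyperresponse group. If individualised dosing after the ovarian reserve test "reduces the rate of OHSS, without affecting live birth rates, individualised treatment is the dominant strategy". The sentence does not say how large a difference in live birth would count as an effect, or how that is to be judged.

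The Statistical analysis section gives the article's one decision criterion: "A probability (p) of less than 0.05 will be considered to be significant". The comparison between arms is made by "applying Chi/square testing to crude rates of cumulative implantation and ongoing pregnancy", together with life table methods.

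On size, the Study design section states "RCT 2 will contain 300 women with an AFC of more than 15". The Sample size calculation section adds "For RCT 2 an increase in pregnancy rate from 35% to 42% over three cycles is expected" and then concedes: "With 300 participants the power to detect this difference is 24" (per cent). The calculations for RCT 1 and for the two trials combined use "alpha-error of 0.05 and a power of 80%, two-sided test". All of these calculations concern a gain. None covers a loss of live births, or the exclusion of one.

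**The concern.** The dominance claim in RCT 2 has two parts: fewer OHSS cases, and live birth left intact. The second part is a claim of absence, and it needs positive evidence that any loss is small. A superiority test that fails to reach significance does not give that evidence, least of all in a comparison with an acknowledged power of 24%.

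Live birth is the primary outcome. A lower stimulation dose could reduce it as well as OHSS, so this condition is the safeguard in the rule. If an undetected loss can pass as no loss, the safeguard is weak. The article also expects its results to inform national and international guidelines, so a wrong statement here would have consequences beyond the trial.

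**Working it through.** **Inputs**
- Control rate 35%, expected individualised rate 42%, 300 women, stated power 24% (Sample size calculation). I treat these as live-birth rates, since the primary outcome is pregnancy resulting in live birth.
- Two-sided 5% level. This is stated for RCT 1 and for the combined calculation, and I assume it for RCT 2.
- Allocation ratio: not stated (women "will be randomly allocated to a standard or individualised FSH regime"). I assume 1:1, so n = 150 per arm.
- Test: chi-square without continuity correction. The article names chi-square for implantation and ongoing pregnancy, and I assume the same test for live birth.
- No dropout applied, as no figure is given.

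**Step 1. Reproduce the stated power**

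Power = Φ{[|p1 − p2|·√n − 1.96·√(2·p̄(1 − p̄))] / √(p1(1 − p1) + p2(1 − p2))}, where p̄ is the mean of p1 and p2.

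35% v 42%, p̄ = 0.385: (0.857 − 1.349)/0.686 = −0.716, so power is 23.7%. Exact enumeration of the uncorrected chi-square gives 23.9%. The stated 24% is reproduced, which supports the 1:1 and two-sided assumptions (a one-sided test would give 34.5%).

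**Step 2. The same test for a loss**
- 35% v 28%, p̄ = 0.315: (0.857 − 1.288)/0.655 = −0.657. Power 25.6%, non-significant 74.4%.
- 35% v 25%, p̄ = 0.30: (1.225 − 1.270)/0.644 = −0.071. Power 47.2%, non-significant 52.8%.

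Chance of a non-significant result at other control rates:

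| Control rate | 7-point loss | 10-point loss |
|---|---|---|
| 30% | 72% | 48% |
| 35% | 74% | 53% |
| 42% | 76% | 57% |

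At a 35% control rate, power reaches 50% at a loss of about 10.4 points and 80% only at about 14.5 points.

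**Step 3. Precision**

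At 35% in both arms, SE = √(2 × 0.35 × 0.65/150) = 0.0551. The 95% half-width is 1.96 × 0.0551 = 0.108, or 10.8 points. An observed difference of exactly zero therefore has a lower limit near −10.8 points.

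**Step 4. What 300 women can show against a margin**

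With equal true rates of 35%, the chance that the lower 95% limit lies above −m is Φ(m/0.0551 − 1.96):
- m = 10 points: Φ(−0.144) = 44%
- m = 7 points: Φ(−0.689) = 25%
- m = 5 points: Φ(−1.052) = 15%

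These margins are illustrations, as the article gives none. For 80% power the totals would be about 716, 1,458 and 2,858 women.

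**The case against.** The strongest reply is that the article never equates an unaffected live-birth rate with p≥0.05. A reader might infer this by joining the Statistical analysis section to the Economic analysis section, but the text does not make that link. The incremental cost-effectiveness ratio in the same section uses the estimated difference in pregnancy rates, and the results feed a decision model. On a point-estimate reading, a true fall from 35% to 28% would show as an observed loss in about 90% of trials: 0.07/√((0.2275 + 0.2016)/150) = 1.31, and Φ(1.31) = 0.90. This stands, and it makes the significance figures conditional. It does not rescue the sentence. An observed difference is almost never exactly zero, so a point-estimate reading also needs a tolerance, and none is given.

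Three stronger conclusions are tempting and not supported:
- **That a real loss would usually lead to a dominance claim.** Dominance also requires reduced OHSS. The article gives no OHSS rate for predicted hyperresponders, so the joint probability cannot be computed from it.
- **That a 10-point loss would probably be missed.** At 53% this is close to a coin toss, and it is 48% with a 30% control rate. Only the 7-point figure is stable.
- **That a margin under about 11 points can never be met.** Whether it is met depends on the observed difference. An observed gain of 1 point gives a lower limit near 1 − 10.8 = −9.8, which clears a 10-point margin.

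The article also discloses the 24% openly and rests its formal power on RCT 1 and the combined 600 women. That is to its credit. But the dominance sentence is specific to predicted hyperresponders, so it rests on RCT 2. Lastly, details of uncertainty analysis may properly sit in a fuller plan that is not shown. The point here is the conclusion rule that the article does state.

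**Conclusion.** The concern holds in a conditional form. The article commits to a dominance conclusion in RCT 2 on a live-birth condition that it leaves undefined. If the condition is judged by the only criterion stated, p<0.05, a true 7-point loss passes it about 74% of the time (72% to 76% for control rates of 30% to 42%). A 10-point loss passes about 53% of the time at the article's 35% control rate. Even an observed difference of zero leaves a loss of nearly 11 points within the 95% interval.

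The figures rest on 1:1 allocation, a two-sided uncorrected chi-square test on live birth and no dropout; the article's 24% supports the first two. They give the chance of passing the live-birth condition, not the chance of declaring dominance. The article's 11-point figure is the gain below which it thinks dose adjustment unlikely to be cost-effective. It should not be taken as a margin for loss.

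**What to change.** In the Economic analysis section:
1. State that a non-significant live-birth difference in RCT 2 will not be taken to show that live birth is unaffected.
2. Claim no relevant loss only if the lower 95% confidence limit of the live-birth difference (individualised minus standard) lies above a margin fixed, with its reason, before outcome data are seen.
3. Otherwise report the difference with its confidence interval, carry that uncertainty into the cost-effectiveness result, and do not call the strategy dominant.
4. State what 300 women can deliver: with equal true rates of 35%, the chance of meeting a 10-, 7- or 5-point margin is about 44%, 25% or 15%.

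No extra women or data are needed. The cost is the wording, agreement on a margin, and a no-loss question added to a trial framed around a gain. The main downside is that RCT 2 may be reported as inconclusive on live birth.
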